#### Reproductive status

7. Number of women with no subsequent pregnancy

i. Voluntary infertility

ii. Involuntary infertility

8. Use of fertility treatments

#### Subsequent pregnancies

9. Number of women having any subsequent pregnancy and for these women, the following outcomes will be measured:

i. Inter-pregnancy interval from the CORONIS birth to the end of the subsequent pregnancy (regardless of loss or birth)

ii. Miscarriage of the pregnancy subsequent to the CORONIS birth

iii. Ectopic pregnancy

For the birth following the CORONIS birth:

iv. Gestation at delivery (by best estimate) of the first viable pregnancy (gestational age > 24 or >28 weeks depending on country specific definition)

v. Stillbirth

vi. Neonatal death

vii. Mode of delivery:

a. Non-instrumental vaginal

b. Instrumental vaginal

c. Pre-labour caesarean section

d. In labour caesarean section

viii. Other pregnancy complications (one or more of the following components: uterine rupture, uterine scar dehiscence, placenta praevia, morbidly adherent placenta, abruption, postpartum haemorrhage requiring transfusion >1 unit of whole blood or packed cells, severe infection within 6 weeks postpartum, hysterectomy up to 6 weeks postpartum, manual removal of placenta)

ix. Bladder or bowel damage at the time of subsequent caesarean section

#### CORONIS children – morbidity and mortality

10. Death or serious morbidity of the child who was born at the time of CORONIS participation.

Parent report of one or more of the following: child's blindness, deafness, inability to speak or walk without assistance, or other major morbidity such as the presence of a stoma. Although no difference in death is expected, there is likely to be a time difference between ‘sharp’ and ‘blunt’ abdominal entry and this may, in theory, lead to more neonatal encephalopathy which may lead to a greater risk of later death.

All outcomes are potentially relevant for each comparison pair; however, some outcomes are more likely to be influenced by some interventions compared with others. Therefore we have categorised comparisons into (i) main comparisons of interest, and (ii) secondary comparisons of interest (Table 1). This approach has been pre-specified to take account of multiple testing and to simplify reporting of the study. Only the main comparisons of interest will be reported in the main paper, although the remaining comparisons will be presented in appendices to ensure transparency and completeness of the analysis.

**Table 1 T1:** **Comparisons of interest** (**M denotes main comparisons of interest**, **s denotes secondary comparisons of interest**)

**Outcome reference number**	**Outcome**	**Bl vs. Sh**	**Ext vs.-A**	**Sl vs. Dble**	**Cl vs. N-Cl**	**Cat vs. P910**
** *Women’s health and mortality* **						
1 i)	Pelvic pain	s	s	s	**M**	s
ii)	Dysmenorrhoea	s	s	s	s	s
iii)	Deep dyspareunia	s	s	s	**M**	s
iv)	Urinary symptoms	s	s	s	s	s
2	Diagnostic laparoscopy or diagnostic laparotomy - not related to pregnancy	s	s	s	**M**	s
3	Hysterectomy or tubal/ovarian surgery - not related to pregnancy	s	s	s	**M**	s
4	Bladder or bowel damage – not related to pregnancy	s	s	s	**M**	s
5 i)	Abdominal hernias	**M**			s	
ii)	Bowel obstruction	s	s	s	**M**	s
6	Woman’s death		s	**M**	s	**M**
** *Reproductive status* **						
7 i)	Women with no subsequent pregnancy – voluntary	s			s	
ii)	Women with no subsequent pregnancy – involuntary	s	**M**	s	**M**	s
8	Fertility treatments	s	**M**	s	**M**	s
** *Subsequent pregnancies* **						
9	Any subsequent pregnancy	s	s	s	s	s
i)	Interpregnancy interval	s	s	s	s	s
ii)	Miscarriage		s	s		s
iii)	Ectopic pregnancy		**M**	s	**M**	s
iv)	Gestation		s	s		s
v)	Stillbirth		s	**M**		**M**
vi)	Neonatal death		s	**M**		**M**
vii)	Mode of delivery		s	**M**		**M**
viii)	Other pregnancy complications (composite of a-i)		s	**M**		**M**
a	Uterine rupture		s	**M**		**M**
b	Uterine scar dehiscence		s	**M**		**M**
c	Placenta praevia		s	**M**		**M**
d	Morbidly adherent placenta		s	**M**		**M**
e	Abruption		s	**M**		**M**
f	Postpartum haemorrhage requiring transfusion of >1 unit of whole blood or packed cells		s	**M**		**M**
g	Severe infection within 6 weeks postpartum		s	**M**		**M**
h	Hysterectomy up to 6 weeks postpartum		s	**M**		**M**
i	Manual removal of placenta		s	**M**		**M**
ix)	Bladder or bowel damage –at the time of subsequent Caesarean section	s	s	s	s	s
** *CORONIS children – morbidity and mortality* **						
10	Death or serious morbidity of CORONIS child	**M**				

Key: Bl vs. Sh = Blunt versus sharp abdominal entry, Ext vs. I-A = Exteriorisation of the uterus for repair versus intra-abdominal repair, Sl vs. Dble = Single versus double layer closure of the uterus, Cl vs. N-Cl = Closure versus non-closure of the peritoneum (pelvic and parietal), Cat vs. P910 = Chromic catgut versus Polyglactin-910 for uterine repair.

### Data collection

Most of the information requested will be provided by the woman at face-to-face interview. Many of the outcomes being collected are clinical diagnoses which are made every day by clinicians in these settings. Women will be asked whether they have pelvic pain and pain on intercourse. Whether or not they have sought or received medical care for their pain will be used as a marker of severity. For women who are pregnant at the time of the follow-up, data will be collected once the pregnancy is over.

For the relatively small number of women who have one of the outcomes resulting in hospitalisation (including subsequent pregnancy complications, such as uterine rupture or dehiscence, hysterectomy, placenta praevia, or other morbidity including non-pregnancy related hysterectomy and laparoscopy/laparotomy), consent will be requested from the women to access their hospital notes, so that additional information relating to the incident can be collected from the relevant hospital by the assessment doctors. Although medical records in some settings in these countries may be poor, this mechanism is being used to seek confirmation of events. We will not use these data as the primary source of the outcome data – these come from the women. In addition any relevant laboratory reports and histopathology will be used by the clinicians reporting morbidity to support their diagnosis. We will collect these data, but we do not require these for confirmation of the diagnosis. For example a post-partum hysterectomy histopathology report will not be required to support a diagnosis of a morbidly adherent placenta but will be used as supportive evidence, if it is available.

### Analysis

A detailed Statistical Analysis Plan (SAP) will be developed and agreed by the Study Steering Committee (SSC) before the analysis is undertaken.

### Analysis populations

For the primary analyses, all maternal and child outcomes will be analysed in the groups into which they were randomly allocated e.g. comparing the outcome of all women allocated “blunt abdominal entry” with all those allocated “sharp abdominal entry”, regardless of technique received. Maternal and child outcomes will be analysed for all eligible women correctly recruited for whom data are available.

The outcomes of interest for women who have a subsequent viable pregnancy, such as uterine rupture, will be analysed using two different denominators i.e. women who subsequently have at least one pregnancy and all women randomised. This will take account of the potential for differences in the pregnancy rate between the two arms being compared.

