#### Women’s health and mortality

1. Following the CORONIS birth and before any subsequent pregnancy, any new onset or worsening of:

i. pelvic pain

ii. dysmenorrhoea

iii. deep dyspareunia

iv. urinary symptoms of poor stream and/or frequency which did not respond to antibiotics

2. Diagnostic laparoscopy or diagnostic laparotomy (not related to pregnancy)

3. Hysterectomy or tubal/ovarian surgery (not related to pregnancy)

4. Bladder or bowel damage in those women who have had surgery, excluding diagnostic laparoscopy and diagnostic laparotomy (not related to pregnancy).

5. Following the CORONIS birth, any new onset of:

i. abdominal hernia

ii. bowel obstruction

6. Woman’s death

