### Sample size and power

The original sample size for the main trial was calculated assuming a 15% primary outcome event rate in the control group (80% power, 5% two-sided significance level, ability to detect a relative risk of 0.85, 15% loss to follow-up) which resulted in a total sample size required of ~ 15,000 women (~ 9,000 in each intervention pair). The actual overall event rate observed during the conduct of the trial was found to be around 9%. The sample size was increased to 15,492 (9,296 per intervention pair) to account for the reduction in the event rate and agreed by the TSC.

Assuming an overall response rate of at least 80% for the follow-up [27,28], this will provide us with information from ~12,400 women (or ~7,400 for each intervention pair). If we assume approximately 80% of these women will have had a subsequent pregnancy this will result in ~5,900 women in each intervention pair. This number will be sufficient to detect modest but clinically important differences between any principal comparison for this population.

The statistical power available, based on a fixed sample size, for a range of event rates on a selection of outcomes is high (Table 2). These incidence rate estimates are based on two follow-up studies of randomised trials, both of which were from developed countries where the event rates are likely to be lower than those observed in the countries participating in CORONIS. These studies, therefore, are likely to represent a conservative estimate of the anticipated event rates. One study was following a trial of closure versus non-closure of the peritoneum [12] and the other following single versus double layer closure of the uterine incision^13^. Both studies were small (n = 145 and 144 women) and the estimates of some of the outcomes are therefore imprecise. For example, the estimate of uterine dehiscence is based on 1 event out of 145 women, giving an incidence of 0.69% with a 95% confidence interval of 0.12% to 3.8%. The estimate of dyspareunia is based on 27 events out of 144 women giving an incidence of 19% with a 95% confidence interval of 13% to 26%.

**Table 2 T2:** power to detect a specified difference for a fixed sample size

**Outcome examples**	**Event rate in 1st group e.g. single layer closure**	**Event rate in 2nd group e.g. double layer closure**	**Absolute risk difference**	**Power available to detect this difference**

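### Bladder or bowel damage (outcome 4) is compared only among operated women, and both denominators for later-pregnancy outcomes need rewording

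*Protocol article*

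**What the plan says.** Three parts of the protocol article bear on this.

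- **Analysis populations, first paragraph.** The general rule is: "Maternal and child outcomes will be analysed for all eligible women correctly recruited for whom data are available".
- **Analysis populations, second paragraph.** This covers "The outcomes of interest for women who have a subsequent viable pregnancy, such as uterine rupture". Such outcomes will be "analysed using two different denominators i.e. women who subsequently have at least one pregnancy and all women randomised". The reason follows: "This will take account of the potential for differences in the pregnancy rate between the two arms being compared".
- **Outcomes, Women's health and mortality.** Outcome 4 reads "Bladder or bowel damage in those women who have had surgery, excluding diagnostic laparoscopy and diagnostic laparotomy", limited to surgery unrelated to pregnancy. In Table 1 the row is shortened to "Bladder or bowel damage – not related to pregnancy", without the surgery condition. It is marked M for closure versus non-closure of the peritoneum and s for the other four pairs. Outcome 3 (hysterectomy or tubal/ovarian surgery) is also marked M for closure versus non-closure.

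Sample size and power supplies the follow-up assumption: "Assuming an overall response rate of at least 80% for the follow-up". The section on primary comparative analyses plans multiple imputation of missing three-year data as a sensitivity analysis.

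**The concern.** **Outcome 4.** Having later surgery is a post-randomisation event. The protocol treats it as a possible effect of peritoneal closure: outcome 3 is a main outcome for that pair, and the Background suggests that non-closure may lead to excessive adhesions. Restricting outcome 4 to operated women therefore compares groups that the technique itself may have selected. An effect that works through the need for surgery can be hidden or even reversed. The article recognises this problem for pregnancy and adds an all-women denominator, but only for later-pregnancy outcomes.

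**Viable versus any pregnancy.** The second paragraph describes outcomes of a viable pregnancy but divides by women with any pregnancy. A woman whose only later pregnancy ended in miscarriage or was ectopic cannot contribute a stillbirth, a neonatal death or a mode of delivery. These are main outcomes for single versus double layer closure and for catgut versus Polyglactin-910.

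**All randomised versus women with data.** Adjacent paragraphs give different populations for the same outcomes. An analyst following the second literally would put women with no information into the denominator.

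**Working it through.** **Reproducing the plan's figures.** Inputs from Sample size and power: 9,296 women per pair, 80% response, and 80% of responders with a later pregnancy.

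- With follow-up data: 9,296 × 0.80 = 7,437 (article: about 7,400).
- With a later pregnancy: 7,437 × 0.80 = 5,949 (article: about 5,900).
- Table 2, rupture or dehiscence, 4% v 5.9%, 5,900 women in equal arms, two-sided 5%: power 92.0% (article: 92%).

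**(a) Outcome 4.** The documents give no rates of surgery or of damage per operation, so both examples below are assumptions. Risk among all women = P(surgery) × P(damage given surgery).

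| Example | | Arm A | Arm B | RR (see below) |
|---|---|---|---|---|
| 1. Effect hidden | Surgery | 4% | 3% | |
| | Damage per operation | 5% | 5% | 1.00 |
| | Damage, all women | 0.04 × 0.05 = 0.20% | 0.03 × 0.05 = 0.15% | 1.33 |
| 2. Effect reversed | Surgery | 1% | 1% + 1% lower-risk | |
| | Damage, all women | 0.01 × 0.10 = 0.10% | 0.0010 + 0.01 × 0.02 = 0.12% | 1.20 |
| | Damage per operation | 10% | 0.0012 / 0.02 = 6% | 0.60 |

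The RR is A/B in example 1 and B/A in example 2. The expected counts are small. At about 3,700 women per arm, example 1 gives 7.4 v 5.6 events and example 2 gives 3.7 v 4.4.

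**(b) Viable pregnancy.** If a share m of women with any later pregnancy had no viable one, a birth outcome's risk on the stated denominator is (1 − m) times its risk among women with a viable pregnancy. The RR shifts only if m differs between arms. The documents give no value for m, so I put no number on this.

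**(c) All women randomised.** Women without data in the literal denominator: 9,296 − 7,437 = 1,859 per pair (20%). The rupture or dehiscence figures then become:

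| Denominator | Risks | RR |
|---|---|---|
| Women with a later pregnancy | 4% v 5.9% | 1.475 |
| Women with data (× 0.80) | 3.20% v 4.72% | 1.475 |
| All randomised (× 0.80 × 0.80) | 2.56% v 3.78% | 1.475 |

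With equal follow-up the RR does not move, and power is 92.2%, 92.0% and 91.7% in turn. With no true effect and loss unrelated to outcome, the all-randomised RR equals the ratio of follow-up fractions, while the RR among women with data stays at 1.00. The splits are assumed: 0.82 / 0.78 = 1.05 and 0.85 / 0.75 = 1.13.

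**The case against.** **On the all-randomised denominator.** A reader might infer that the plan counts women lost to follow-up as event-free. The documents do not support that. No sentence says so, and the general rule limits analysis to women with data. Table 2 uses the label of all women for the roughly 7,400 expected responders, not the 9,296 randomised. Imputing missing data as a sensitivity analysis also fits poorly with such a rule. The second denominator is there to handle differing pregnancy rates, not missing data. Nor does the article predict differential loss: contact is organised by regional office, and losses will be reported by pair. This objection largely stands. What remains is a conflict in wording that could be misapplied.

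**On the pregnancy denominators.** One might complain that a subset of women with a pregnancy is not randomised, or that neither denominator is named as primary. The first is already met by adding an all-women denominator. The second can properly be left to the SAP, which is not shown.

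**On outcome 4.** It is a main comparison for one pair of five, and outcome 3 will be reported beside it, so a change in gynaecological surgery would be visible. Events would be few, and the reversal rests on assumed rates. All true, but outcome 3 covers only part of the surgery that qualifies a woman for outcome 4. Reporting the two side by side does not turn a comparison of operated women into a randomised one. The other bladder or bowel outcome (9 ix, at repeat caesarean) is secondary throughout and plausibly already falls under the two-denominator rule, so it adds nothing to the concern.

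**Conclusion.** The point holds in three limited parts.

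1. **Outcome 4, closure versus non-closure.** As defined, this main comparison is not between randomised groups, and no all-women denominator is provided for it. This follows from the definitions alone. The size does not: 1.00 v 1.33, or a reversal from 1.20 to 0.60, are illustrations under assumed rates.
2. **Viable pregnancy.** The conditional denominator does not match its outcomes. The effect on absolute risks depends on a share the documents do not give.
3. **All women randomised.** This phrase conflicts with the restriction to women with data. Taken literally at 80% response, it lowers absolute risks by a fifth, but only for later-pregnancy outcomes on that one denominator. The relative risk is biased only if follow-up differs between arms (1.05 to 1.13 over the assumed splits).

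None of this shows that the plan sets missing outcomes to no event, and it does not undermine the Table 2 power figures.

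**What to change.** - **Outcome 4:** make the main analysis the proportion with bladder or bowel damage among all eligible randomised women with follow-up data. Keep the result in operated women as supplementary and label it non-randomised. Bring the outcome list and the Table 1 row into line.
- **Conditional denominator:** replace women with at least one pregnancy by women with at least one subsequent viable pregnancy for the viable-pregnancy outcomes.
- **Second denominator:** restate it as all eligible randomised women with follow-up data, with the planned multiple imputation as the sensitivity analysis for the rest.

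The cost is a few lines in the protocol and SAP. No new data are needed and no planned result is lost. The drawback is that outcome 4 will show very low percentages, so counts should be printed beside them.

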### Descriptive analyses

The flow of participants through each stage of the trial will be illustrated in a CONSORT flowchart [24,25]. This will include the numbers (with percentages) of losses to follow-up over the period of the follow-up study (including reasons, where known) by pair of interventions.

Baseline demographic and clinical characteristics will be described separately for the five intervention pairs in the main trial publication, for those women for whom follow-up data are collected. We will compare the characteristics of such women with those for whom no follow-up assessment was possible using tests of statistical significance, overall and by pair of interventions.

### Primary comparative analyses

The primary analyses will be performed on each of the five pairs of surgical techniques. Outcomes will be summarised by intervention group using appropriate summary statistics (counts and percentages, means and standard deviations, or medians and inter-quartile ranges). Comparisons will be made using relative risks (RR) for dichotomous/categorical outcomes, mean differences for normally distributed continuous outcomes, or median differences for skewed continuous variables (unless the data can be transformed to normality). Analysis of time to event outcomes will employ survival analysis techniques [26].

Multiplicity of statistical testing will be addressed in the detailed statistical analysis plan.

With regard to the analysis of child outcomes, multiple births will be treated as independent events in the primary analysis, in order that relative risks may be presented.

Adjusted analyses will be performed on all comparisons to investigate the impact of minimsation factors ‘In-labour or not in-labour caesarean section’ and ‘number of previous caesarean sections (none or one)’. These will be agreed by the investigators and the Study Steering Committee and pre-specified in the SAP.

Subgroup analyses will be similarly agreed and pre-specified in the statistical analysis plan and results will be presented on forest plots, by intervention pair, wherever appropriate.

The robustness of the results will be examined in sensitivity analyses by using multiple imputation techniques to impute missing 3 year follow-up data, and also restricting analyses to a pre-specified follow-up window. Sensitivity of the effect estimates to adjustments for potential clustering of multiple births will also be examined.

Interactions will be explored using a structured approach. Plausible interactions are difficult to identify and not all can be assessed due to the nature of the trial design. A strategy for the analysis of interactions for the main trial has been agreed by the Trial Steering Committee to prevent the investigators being misled by spurious interactions, given the multiplicity of possible explorations. This strategy will be employed for the primary analysis of the follow-up study i.e. analyses of interactions will only be performed on the main comparisons; and three-way interactions will not be investigated unless there is strong evidence of a two-way interaction in the presence of main effects. The results of the exploration of interactions will be interpreted cautiously together with other evidence such as biological plausibility and consistency (e.g. across countries). Plausible interactions for each outcome will be agreed by the investigators and the Study Steering Committee and pre-specified in the SAP.

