### Trial eligibility

Women are eligible for trial entry if they are undergoing delivery by lower segment caesarean section through a transverse abdominal incision, irrespective of fever in labour, gestational age or whether they have a multiple pregnancy.

Women are not eligible if: (i) there is a clear indication for a particular surgical technique or material to be used that prevents any of the allocated interventions being used; (ii) they have had more than one previous caesarean section; (iii) they have already been recruited into the trial during a previous pregnancy.

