**For women who have a subsequent pregnancy (number estimated to be ~5,900)**				
Uterine rupture or dehiscence	4%	5.9%	1.9%	92%
Preterm birth	10%	7.5%	2.5%	93%

The power calculations in Table 2 assume equal numbers in each comparison and a 2-5% level of statistical significance.

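### The reason given for treating multiple births as independent in the primary child analysis is not valid: a relative risk with mother-clustered standard errors is available, and the effect on the interval is small

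*Protocol article*

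**What the plan says.** Four statements in the Protocol article bear on this.

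- **Effect measure** (Primary comparative analyses): "Comparisons will be made using relative risks (RR) for dichotomous/categorical outcomes".
- **Multiple births, primary analysis** (same section): "multiple births will be treated as independent events in the primary analysis, in order that relative risks may be presented". No other reason is offered.
- **Multiple births, sensitivity analysis** (same section): "Sensitivity of the effect estimates to adjustments for potential clustering of multiple births will also be examined".
- **Eligibility** (Trial eligibility): women may enter "irrespective of fever in labour, gestational age or whether they have a multiple pregnancy".

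The child outcome is number 10: "Death or serious morbidity of the child who was born at the time of CORONIS participation". Table 1 marks it as a main comparison for blunt versus sharp abdominal entry and leaves the other four columns blank. The only other main comparison for that pair is abdominal hernia.

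**The concern.** The woman is the randomised unit, so twins always share an allocation. They also share a mother, a pregnancy and a delivery, so a positive correlation in their outcomes is plausible. Counting them as separate independent observations then claims a little more information than the data hold.

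The article accepts this for the sake of reporting relative risks. That trade is unnecessary, because allowing for clustering does not prevent a relative risk from being reported. The variance that allows for siblings is left to a sensitivity analysis, while the interval and p-value reported first use the one that does not.

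At stake is the stated precision of one of the two main comparisons for blunt versus sharp entry. Its estimate is not in question.

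**Working it through.** **Is there a figure to reproduce?** The article gives none for the child analysis: no twin rate, within-pair correlation, child event risk or power.

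**Nominal level.** The article says "The power calculations in Table 2 assume equal numbers in each comparison and a 2-5% level of statistical significance", which is not a single level. At two-sided 5% with equal groups, the five powers in Table 2 come out at 92.5, 93.2, 92.5, 92.0 and 92.5%, against 92, 93, 92, 92 and 93% printed. At 2% they fall to 85-87%. I therefore use two-sided 5%.

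**Step 1: can a relative risk be reported with clustering allowed for?** Fit a Poisson log-link model with allocation as the only covariate, children as observations and a sandwich variance clustered on the mother. The exponentiated coefficient is the ratio of the two observed proportions, which is the simple relative risk. In simulated data the two agreed to within about 2.5e-11. Only the standard error (SE) changed. The stated reason therefore fails.

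**Step 2: size, with equal risk in twins and singletons.** Let m be the proportion of mothers with twins and ρ the within-pair correlation. Per mother there are 1 + m children, of whom 2m are twins, and each pair's variance is multiplied by 1 + ρ. So

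Design effect = 1 + ρ × 2m/(1 + m)

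SE factor = √(design effect)

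Type I error = 2 × [1 − Φ(1.96/SE factor)]

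| m (assumed) | ρ (assumed) | Twin share of children, 2m/(1+m) | Design effect | SE factor | Type I error |
|---|---|---|---|---|---|
| 2% | 0.3 | 0.0392 | 1.012 | 1.006 | 5.1% |
| 3% | 0.5 | 0.0583 | 1.029 | 1.014 | 5.3% |
| 5% | 0.8 | 0.0952 | 1.076 | 1.037 | 5.9% |

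The naive SE is short by 1 − 1/1.006 = 0.6% in the first row and 1 − 1/1.037 = 3.6% in the last.

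**Step 3: higher risk in twins.** Write V for each group's share of the independence variance. Then design effect = [V_single + V_twin(1 + ρ)]/[V_single + V_twin]. Assume singleton risk 2%, m = 2%, ρ = 0.5 and threefold risk in twins:

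- V_single = 0.98 × 0.02 × 0.98 = 0.01921
- V_twin = 2 × 0.02 × 0.06 × 0.94 = 0.00226
- Design effect = 1 + 0.5 × 0.00226/0.02147 = 1.053, so the SE factor is 1.026

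With equal risk the factor would be 1.010. Over a wide assumed range (m 1-5%, ρ 0.1-1.0, twin risk 1 to 5 times the singleton risk) the SE factor runs from 1.001 to 1.15 and type I error from 5.0% to 8.9%. The top requires the highest value of all three inputs together.

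**Step 4: simulation.** The article expects "or ~7,400 for each intervention pair", so I take 3,700 women per arm. Settings are 20,000 replicates, two seeds, singleton risk 2% and ρ = 0.5.

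| Twin pregnancies | Twin risk vs singleton | Robust/naive SE | Type I, naive | Type I, clustered |
|---|---|---|---|---|
| 2% | 1× | 1.010 | 5.0-5.1% | 4.8% |
| 2% | 3× | 1.027 | 5.5-5.6% | 4.8-5.1% |
| 3% | 3× | 1.038 | 5.5-5.6% | 4.7-4.8% |
| 5% | 5× | 1.084 | 7.0-7.1% | 4.9-5.0% |

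The clustered SE matched the empirical spread of the log relative risk to within about 0.5%.

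**The case against.** The best defence is that the plan has already seen the issue. The clustering-adjusted analysis is pre-specified in the same section, so the dispute comes down to which of two planned analyses is labelled primary, plus one clause of rationale. The shift is small, most mothers contribute one child, and one outcome in one column of Table 1 is affected. Multiplicity is deferred to the statistical analysis plan, so the article fixes no 5% decision rule for this outcome that such a shift would overturn. Analysing children as independent first also keeps the relative risk consistent with the raw counts.

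Most of this stands, and it is why the point is minor. Two parts do not rescue the wording:

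- The mother-clustered relative risk is also the ratio of the raw proportions, so consistency with the counts is no reason to prefer the naive variance.
- The sensitivity analysis leaves the primary interval and p-value on the naive variance. It is also phrased around the effect estimates, and under a cluster-robust variance the estimate does not move. The comparison that matters is between the intervals.

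A reader might go further and infer that the independence assumption is false by design, or that deaths and serious morbidity will be concentrated in multiples so that clustered events dominate. The documents do not support either reading. Shared allocation follows from the design, but the interval is too narrow only if the within-pair correlation is positive, and no correlation is given. Nor is there any twin rate or child risk. Higher twin risk appears above only as an assumption.

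**Conclusion.** The point holds in a limited form. The stated reason for assuming independence is wrong, and this can be shown without any assumption. The consequence is a primary interval for "Death or serious morbidity of CORONIS child" that is slightly too narrow if siblings' outcomes are positively correlated. The likely size is an SE understated by about 0.6-4% and a type I error of about 5.1-5.9%, assuming 2-5% twin pregnancies, correlation 0.3-0.8 and equal risk. It grows if twins have higher risk, but reaches 8-15% of the SE only with a high twin rate, high twin risk and strong correlation together.

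The relative risk itself and all maternal outcomes are unaffected. A reader might infer that stillbirth and neonatal death at the next birth, which are main comparisons for two other pairs, are affected as well. Table 1 lists those under subsequent pregnancies, and the article does not say whether the multiple-birth rule reaches them, so I do not count them. The finding does not threaten the validity of the study.

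**What to change.** In Primary comparative analyses, delete the clause that justifies independence by the wish to present relative risks. Replace the sentence with one to this effect: child outcomes will be compared by log-link regression with robust standard errors clustered on the mother, giving relative risks that allow for multiple births. Keep the independence analysis as the sensitivity analysis, and compare the confidence intervals as well as the estimates.

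The cost is one or two sentences. The change uses standard software, needs no new data and leaves the relative risk the same. Because the article says the detailed statistical analysis plan is still to be agreed before analysis, the correction can be made there.
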